### Quality of Life

Participating patients are asked to complete three questionnaires pre- and postoperatively during the follow-up period, the SF-36, OBESI-Q, and GERD-HRQoL, to assess quality of life.

The SF-36 questionnaire includes 36 items and measures eight health concept scales: Physical Functioning, Role-Physical, Bodily Pain, General Health, Vitality, Social Functioning, Role-Emotional, and Mental Health. The raw scores of each subscale are transformed to a 0–100 scale, where higher scores indicate better functioning or well-being. A minimum of 50% of the items in each subscale must be answered to yield a viable result [17].

The OBESI-Q questionnaire includes a set of six selected subscales from the BODY-Q that have been individually validated for Dutch practice [18, 19]. The BODY-Q measures four overarching domains. Each domain includes four or more independently functioning scales. Scales chosen in OBESI-Q include eating behavior, social, psychological, physical function, body image, and sexual. Scores for each outcome are calculated by summing up the points for each subscale. To enhance the interpretability of the sum score, it is converted to a total score on a scale of 0 to 100, where higher scores indicate better functioning or well-being.

The GERD-HRQoL questionnaire includes 18 items to measure the impact of GERD on sleep, exercise, diet, need for medication, sex life, work, social activity, and psychological well-being [20]. The total score is calculated by summing up the individual item scores, with no transformation of the raw scores into a scaled score required. The optimal score is 0, which indicates that the individual is asymptomatic across all categories, while the lowest possible score is 50, indicating complete incapacitation in all categories.

### Surgical Techniques

Standard surgical techniques are used in all study patients. A long and narrow pouch is formed from the angle of the lesser curvature to the angle of His. Calibration of pouch diameter is done loosely around a 34 fr nasogastric tube. A standard-length biliary limb of 150 cm for patients with BMI up to 50 kg/m^2^ or 180 cm for patients with BMI above 50 kg/m^2^ is drawn cranially in an antecolic antegastric position. A 30/40-mm stapled side-to-side gastro-jejunostomy is created with a linear endostapler. The remaining defect is closed with a 23-cm 3–0 absorbable V-loc running suture, starting the suture more proximally on the biliary limb and aligning this along the longitudinal stapling line of the pouch. In the intervention group, a silicone ring is placed 2 to 4 cm caudal to the gastro-esophageal junction. The chosen circumference of the silicone ring is 7.5 cm (approximately 24 mm internal diameter). The silicone ring is secured to the longitudinal staple line with a non-absorbable suture. Control of the integrity of the anastomosis and staple line is performed in both groups by air leak testing after the introduction of a gastric tube by the anesthesiologist. Additional sutures are placed in case of leakage.

The silicone ring is a CE-marked medical device by Bariatric Solutions, which consists of a silicone-coated blunt tip and a ring body with four locking positions. Once the ring is secured, the blunt tip will be cut off and removed.

### Sample Size Calculation

In order to obtain mid-term results, a 5-year follow-up period has been selected, consistent with standard practices in Dutch metabolic bariatric surgery. A total of 63 patients per group is necessary to detect a 5% difference %TWL between groups 5 years post-surgery. This calculation is performed using PASS software, with parameters set at power = 80%, alpha = 0.05, standard deviation = 10%, and average %TWL of group 1 vs. group 2 being 32 vs. 27, assuming a two-sided independent *t*-test.

Jense et al. observed a loss-to-follow-up (LtfU) ranging from 21 to 58% three to five years postoperatively [21]. To have sufficient power for the 5-year analysis, this study takes into account a LtFU of 40%, assuming that actively contacting patients will reduce LtFU at 5 years postoperatively. Based on a required sample of 63 individuals per group and an expected LtFU of 40%, we aim to include 210 patients for this study, 105 per group.

## Outcome Measurement

All outcomes are measured at 4 months and annually up to 5 years postoperatively.

### Primary Outcome

%TWL is defined as the percentage of weight loss relative to the total body weight at the time of informed consent [22]. In formula$${\%}TWL=\frac{\text{preoperative weight}-\text{ postoperative followup weight}}{\text{preoperative weight}}\text{x}\;100$$

### Secondary Outcomes

%EWL: defined as the percentage of excess weight lost relative to the excess weight at the time of informed consent [22]. In formula$${\%EWL}=\frac{\text{preoperative BMI}-\text{ current BMI}}{\text{preoperative BMI}-25}\text{x}\;100$$Reduction or remission of obesity complications: Obesity complications include type 2 diabetes mellitus, hypertension, joint complaints, dyslipidemia, OSAS, and GERD. (Inter)national guidelines are used as reference [23, 24]. Reduction is defined as a decrease in symptoms, medication use and/or dosage, and/or laboratory results. Remission is defined as the state in which a patient no longer reports symptoms, does not require any medication for their comorbidity, and/or has normalized laboratory results. In case of type 2 diabetes, remission is defined if glycosylated hemoglobin (HbA1c) is 43 mmol/mol without the use of pharmacotherapy as per local protocol [23] In case of OSAS, remission is considered when there is a discontinuation of CPAP treatment.Quality of life: assessed using the SF-36, OBESI-Q, and GERD-HQoL questionnaires at earlier mentioned follow-up intervals compared to pre-operative baseline measurements.Presence of early and late dumping: determined based on symptoms reported by patients and evaluated by expert physicians during the follow-up period.Complications: All complications during follow-up and until 5 years postoperative are included in the analysis, regardless of their potential relation to the ring. Complications are categorized as perioperative, early (< 30 days, with or without readmission), and late (> 30 days, with or without readmission). Possible complications include bleeding, wound infections, intra-abdominal abscesses, anastomotic leaks, deficiencies (especially in vitamin B12 and ferritin), conversions, migration, erosion, and slipping of the ring. Laboratory reference values are used for deficiencies.

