## Methods

### Study Design and Patient Selection

This study is a single-center, non-blinded, prospective randomized controlled trial. The intervention group consists of patients undergoing standard OAGB with the addition of a MiniMizer silicone Ring (Bariatric Solutions GMBH, CH-8260 Stein am Rhein), placed 2 to 4 cm below the esophagogastric junction (see the “Surgical Techniques” section). The control group consists of patients undergoing standard OAGB without the addition of the silicone ring. All procedures will be performed by one of five bariatric surgeons. Of these, two surgeons will exclusively perform standard OAGB in the control group, while the other three surgeons will conduct both the intervention and standard procedures.

Patients meeting the general (inter)national criteria for MBS [4] are potentially eligible for participating in this study. Exclusion criteria are shown in Table 1. Patients are informed about the study during their preoperative screening. Participation is voluntary, and patients are offered a 2-week period to consider their decision before signing the informed consent form.

**Table 1 Tab1:** Exclusion criteria

Previous MBS
Insufficient proficiency in the Dutch language
Genetic conditions affecting compliance with medical advice
Chronic inflammatory bowel diseases
Renal dysfunction (eGFR < 30) or liver dysfunction (ASAT/ALAT twice the normal values)
Pregnancy before or during the study
Clinically severe therapy-resistant GERD
Silicone allergy

After providing informed consent, patients are randomly assigned to one of the two groups using a computer-generated randomization sequence to ensure balanced allocation.

All patients will receive standard multidisciplinary pre- and postoperative care, in accordance with the local standards of care. This includes preoperative blood tests and the “Modifast Intensive®” diet for 2 weeks, providing 850 kcal/day to reduce liver volume, promote weight loss, and improve surgical conditions and recovery [16]. Postoperative care is provided for 4 months, followed by annual evaluations for up to 5 years, including blood tests and assessment of obesity complications. In this study, patients will also complete standardized questionnaires in addition to the standard care (see the “Quality of Life” section).

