### Statistical Analysis

IBM’s Statistical Package for the Social Sciences (SPSS) is utilized for the statistical analyses of the obtained data. Histograms (visual inspection) are used to ascertain whether variables are normally distributed. A significance level (alpha) of 0.05 is applied to all analyses unless stated otherwise. Differences in baseline characteristics of the study groups are tested using the independent *t*-test (for continuous, normally distributed data), the Mann–Whitney test (for non-normally distributed or ordinal data), or the chi-square test (for categorical data).

Assumptions for linear regression will be checked for all outcomes, including normality of residuals and homogeneity of variances. Where necessary, transformations (e.g., log transformation) were applied to meet model assumptions.

Difference between groups in %TWL, %EWL, and GERD-HRQoL at 5 years postoperative will be assessed using the independent *t*-test or Mann–Whitney test (for normally or non-normally distributed data, respectively). Baseline characteristics related to both the type of surgery and outcome variables (with *p*-value < 0.15) will be considered confounders in the analyses. If one or more confounders are identified, linear regression models will be used to assess differences between groups in %TWL, %EWL, and GERD-HRQoL at 5 years postoperative, each adjusted for relevant confounders.

The difference between groups in the reduction of obesity complications at 5 years postoperative will be tested using chi-square tests for each comorbidity. Holm-Bonferroni correction will be used to correct for multiple testing.

Chi-square tests will be used for the difference between groups in change of scores of the questionnaires, early and late dumping, and reflux. Additionally, a linear mixed model analysis will test the difference in change in the subscales of the SF-36 and OBESI-Q over time between groups.

The difference in the total number of complications between groups will be tested with independent *t*-tests or Mann–Whitney tests (for normally or non-normally distributed data, respectively).

Missing data will be reported if known. A sensitivity analysis will be performed for the primary outcome: analysis of the data “as-is” (without imputation) will be compared with the results of the analysis where missing data is imputed.

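### A complication counts as reduced on any decrease, of any size, in any one component, so unchanged or treatment-escalated patients can count as responders and the 5-year comparison is diluted

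*Protocol article*

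**What the plan says.** Secondary Outcomes in the protocol article lists six conditions: "Obesity complications include type 2 diabetes mellitus, hypertension, joint complaints, dyslipidemia, OSAS, and GERD". It refers to national and international guidelines and then gives its own rule: "Reduction is defined as a decrease in symptoms, medication use and/or dosage, and/or laboratory results". Remission is defined separately. It has specific criteria for two conditions: an HbA1c value without drug treatment for type 2 diabetes, and for sleep apnea "In case of OSAS, remission is considered when there is a discontinuation of CPAP treatment". No such condition-specific criteria are given for reduction.

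Statistical Analysis says: "The difference between groups in the reduction of obesity complications at 5 years postoperative will be tested using chi-square tests for each comorbidity", followed by "Holm-Bonferroni correction will be used to correct for multiple testing". Study Design and Patient Selection describes the trial as non-blinded.

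**The concern.** The rule is stated, and as stated it is loose in two ways.

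- **No minimum change.** A laboratory value marginally below baseline is a decrease. Where the marker is continuous, a patient with no real change will often meet the rule by chance.
- **No condition on the other components.** The components are joined so that one is enough. A patient whose marker fell because medication was increased meets the rule on the laboratory component, although the disease needed more treatment.

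Both faults add responders who have not improved. If that happens equally in the two arms, the observed difference shrinks and both reduction rates look better than they should. In a non-blinded trial, a rule that any reported decrease in symptoms can satisfy alone is also open to expectation effects, which need not be equal between the arms.

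**Working it through.** **The plan's own figure.** The article gives no sample size or power for this outcome. Its only calculation is for %TWL: a difference of 5, SD 10, two-sided alpha 0.05 and 80% power. The normal approximation gives 63 per group, and 63/0.60 = 105 per group or 210 in total, as stated. This point does not affect that figure. It supplies the 63 evaluable patients per arm used below.

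**Step 1: chance that an unchanged patient qualifies.** With independent components, q = 1 − Π(1 − qᵢ). The article gives none of the qᵢ, so these are assumptions: laboratory value lower by chance 50% (symmetric noise, no ties), symptoms reported lower 10–25%, medication or dose lower 5–10%.

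| Components that apply | Low inputs | High inputs |
|---|---|---|
| Laboratory, symptoms, medication | 1 − 0.50 × 0.90 × 0.95 = 57% | 1 − 0.50 × 0.75 × 0.90 = 66% |
| Symptoms, medication only | 1 − 0.90 × 0.95 = 14.5% | 1 − 0.75 × 0.90 = 32.5% |

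The first row clearly fits type 2 diabetes and dyslipidemia. The second fits joint complaints, OSAS and GERD. It also fits hypertension unless blood pressure is treated as a qualifying result, which the wording does not say.

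*Independence.* If chance falls overlap completely, q is the largest single qᵢ: 50% in the first row and 10–25% in the second. If they never coincide, the qᵢ add: 0.50 + 0.10 + 0.05 = 65% to 0.50 + 0.25 + 0.10 = 85% in the first row, and 15–35% in the second. The contrast between the rows remains.

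**Step 2: effect on the difference.** Let p₁ and p₂ be the true proportions improved, let all truly improved patients be counted, and let q be equal in both arms. The observed proportion is p + (1 − p)q, so the observed difference is (p₁ − p₂)(1 − q). This holds for any p₁, p₂ and q.

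**Step 3: illustration.** Assume true reduction of 85% vs 70%. Power uses the normal approximation Φ[(d − 1.96·SE₀)/SE₁], with SE₀ = √(2p̄(1 − p̄)/n), SE₁ = √((p₁(1 − p₁) + p₂(1 − p₂))/n), n = 63 per arm and alpha 0.05 before Holm correction. Without dilution, SE₀ = √(2 × 0.775 × 0.225/63) = 0.0744, SE₁ = √((0.1275 + 0.21)/63) = 0.0732, and power is Φ[(0.15 − 0.1458)/0.0732] = 52%.

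| q | Observed proportions | Difference | Power |
|---|---|---|---|
| 0 | 85.0% vs 70.0% | 15.0 points | 52% |
| 14.5% | 87.2% vs 74.4% | 12.8 points | 45% |
| 32.5% | 89.9% vs 79.8% | 10.1 points | 35% |
| 57% | 93.6% vs 87.2% | 6.4 points | 23% |
| 66% | 94.9% vs 89.9% | 5.1 points | 19% |

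A second assumed scenario, 70% vs 50%, behaves the same way: power is 63% with no dilution, 29% at q = 50% and 15% at q = 75%. All these powers are generous, because only patients who have the condition at baseline can be reduced, so n per test will be below 63.

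**The case against.** The strongest reply is that the article condenses a fuller protocol and cites guidelines as its reference, so thresholds and conflict rules may exist there. That would answer a complaint about a missing definition. Here a definition is given, and nothing says that the guidelines override it or supply a minimum change for reduction. The reply leaves open that practice may be stricter than the text.

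Second, the secondary outcome combines reduction and remission, so the word used in Statistical Analysis may be shorthand for both. That is a fair reading. It does not remove the fault, since the loose category would still feed the tested proportion, but the text should say which is meant.

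Third, these are secondary comparisons that were never powered, and they are weak even without dilution (52% in the illustration). That stands and limits the importance of the point.

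Stronger readings that a reader might infer are not supported:

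- *Most unchanged patients qualify.* Under the assumed inputs this is so only with a continuous laboratory marker. For conditions judged on symptoms and medication, q is about 15–33%.
- *Both arms sit near the ceiling and no difference can be shown.* The article gives no response rates, and the illustration still leaves 5 to 13 points.
- *A fall in HDL cholesterol would count as improvement.* This is too literal. In a sentence defining improvement, the natural meaning is a change toward normal. Stating the direction per marker settles it.
- *The plan intends to count escalated patients as reduced.* It does not say so. The text is silent, and the result follows only from its literal wording.

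**Conclusion.** The concern holds in this limited form. The stated rule accepts a decrease of any size in any one component and has no provision for components that move in opposite directions. Patients with no real improvement, or whose treatment was escalated, can therefore count as responders. The (1 − q) shrinkage is exact when q is equal in both arms and true improvers are all counted. The values of q are assumptions. With them, between about one seventh and one third of the true difference is lost where only symptoms and medication apply, and somewhat more than half to two thirds where a continuous laboratory marker applies. The consequences are lower power and overstated reduction rates in both arms. If q differs between arms, as it could without blinding, the difference could be biased in either direction, and the article gives no means to size that. The primary endpoint and its sample size are untouched. This should be corrected, but it does not threaten the trial's main conclusion.

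**What to change.** In Secondary Outcomes, restrict the analysis to patients with the condition at baseline. Score a complication as reduced only if all of the following hold:

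1. At least one component relevant to that condition (symptoms, medication or marker) improved. For continuous markers, a minimum change and its direction are stated in advance.
2. No other component is worse.
3. Treatment for that condition was not escalated.

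Score all others as unchanged or worse. Keep symptoms as a qualifying component for joint complaints, OSAS and GERD, which have no laboratory marker; otherwise a patient with real symptom relief and no medication to reduce could never qualify. A comparison across remission, reduced, unchanged and worse is optional, since it spreads small subgroups thinner.

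In Statistical Analysis, say whether the tested outcome is reduction alone or reduction plus remission.

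Fix the wording before the 5-year data are examined by arm, so that the choice of rule cannot be questioned later. The cost is mainly drafting, since complications and blood tests are already assessed annually. Confirm that medication use and dose, and blood pressure if it is to be used, are recorded at those visits, because the article does not say so explicitly. The downsides are lower headline response rates and slightly more classification work.

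### The OSAS remission rule counts stopping CPAP for any reason and is not reconciled with the general remission definition beside it

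*Protocol article*

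**What the plan says.** Secondary Outcomes lists six obesity complications, OSAS among them, cites guidelines as reference, and defines two outcomes for all of them.

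- **Reduction:** "Reduction is defined as a decrease in symptoms, medication use and/or dosage, and/or laboratory results".
- **Remission:** "Remission is defined as the state in which a patient no longer reports symptoms, does not require any medication for their comorbidity". An and/or clause then brings in normal laboratory values.

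Two condition-specific sentences follow, one for type 2 diabetes and one for OSAS. The OSAS sentence reads: "In case of OSAS, remission is considered when there is a discontinuation of CPAP treatment".

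Statistical Analysis then says: "The difference between groups in the reduction of obesity complications at 5 years postoperative will be tested using chi-square tests for each comorbidity". It adds: "Holm-Bonferroni correction will be used to correct for multiple testing". The sentence on testing names reduction; it does not mention remission. On masking, Study Design and Patient Selection says: "This study is a single-center, non-blinded, prospective randomized controlled trial".

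**The concern.** The OSAS sentence is a stated rule, so this is not detail that an article would leave to a fuller document. The rule measures what the patient does with a device. It does not ask whether symptoms have gone, or why the device was given up. Stopping because CPAP is no longer needed and stopping because the mask is not tolerated receive the same score.

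The general definition next to it does look at symptoms, but the article does not say whether the OSAS sentence replaces that definition, offers a second route to remission, or adds a condition. Two assessors could therefore score the same patient differently.

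At stake is the OSAS remission rate in each arm and the contrast between arms. Because patients know their allocation, the decision to stop CPAP may itself depend on it.

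**Working it through.** **1. The plan's own figures.** The article gives no figure for OSAS. Its only sample-size figure concerns %TWL: 2 × (1.96 + 0.84)² × (10/5)² ≈ 63 per group, and 63/(1 − 0.40) = 105 per group. Both reproduce, and this point does not touch them.

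**2. The two definitions side by side.** The table applies each possible relation between the OSAS sentence and the general definition to two kinds of patient. It takes absence of symptoms as a necessary part of the general definition.

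| Relation | Stops CPAP from intolerance, symptoms persist | No CPAP at baseline, symptoms gone |
|---|---|---|
| OSAS sentence replaces the general definition | Remission | Nothing to discontinue; status undefined |
| OSAS sentence is an alternative route | Remission | Remission through the general definition |
| OSAS sentence is an added condition | Not remission | CPAP condition cannot be met as worded |

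The first two relations score the intolerant patient as a success. The third avoids that, but leaves the patient without baseline CPAP unable to qualify on the wording. No relation handles both patients sensibly, and the article does not choose among them.

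**3. Equal stopping in both arms (illustration).** Let p be the true remission proportion among baseline CPAP users and q the fraction of non-remitters who stop CPAP for other reasons. Then:

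- observed remission = p + (1 − p)q
- observed difference = (p₁ − p₂)(1 − q)

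All values of p and q are assumptions.

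| True rates | q | Observed rates | Difference (points) |
|---|---|---|---|
| 70% vs 50% | 0.1 | 73% vs 55% | 20 → 18 |
| 70% vs 50% | 0.2 | 76% vs 60% | 20 → 16 |
| 70% vs 50% | 0.3 | 79% vs 65% | 20 → 14 |
| 60% vs 45% | 0.2 | 68% vs 56% | 15 → 12 |
| 60% vs 45% | 0.3 | 72% vs 61.5% | 15 → 10.5 |
| 60% vs 45% | 0.4 | 76% vs 67% | 15 → 9 |

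In the last three rows the reported rates are too high by 8 points (60% to 68%) up to 22 points (45% to 67%).

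**4. Unequal stopping (illustration).** Suppose true remission is 50% in both arms, with q = 0.3 in one and 0.1 in the other. Observed rates are 0.50 + 0.50 × 0.3 = 65% and 0.50 + 0.50 × 0.1 = 55%, a spurious 10 points. Exchanging the two q values reverses the sign. The direction therefore cannot be known in advance.

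**5. How much information the comparison carries.** Take the 63 completers per arm and assume that 15%, 25% or 40% have OSAS. That gives 9.4, 15.8 or 25.2 patients per arm. For 70% vs 50%, normal-approximation power at two-sided 0.05, before Holm-Bonferroni, is about 14%, 20% or 30% with q = 0. With q = 0.3 it is about 10%, 14% or 19%. This models a remission comparison, which Statistical Analysis does not name as a test.

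**6. Route into the named test.** Reduction is defined through symptoms, medication and laboratory results, and CPAP is neither a medication nor a laboratory result. A false remission would enter the chi-square test only if remission is also counted as a reduction. The article does not say whether it is.

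**The case against.** The best defence is that the article does not say the OSAS sentence cancels the general definition. It can be read as extending a rule about medication and laboratory results to a condition treated with a device, with cited guidelines behind it that are not shown. That stands in part. A reader might infer that stopping CPAP is the sole criterion, and the text does not establish that. It does not remove the fault, because an alternative route to remission still admits the intolerant patient with symptoms.

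A reader might also infer that OSAS patients without CPAP at entry cannot be classified at all. That goes too far. They can be scored for reduction through a decrease in symptoms, and on one reading for remission through the general definition. Only their remission status is unclear.

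Nor is it an error that a patient who keeps using CPAP after recovery is not counted as in remission. That is a conservative choice, in keeping with the idea that remission means no continuing treatment.

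It is also fair to say that the test sentence names reduction alone, that every p and q above is assumed, and that dilution and differential stopping can pull in opposite directions. All of this stands, and it rules out any claim about the size or net direction of bias in the trial's planned test.

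Finally, a remedy resting only on the treating physician's opinion that CPAP is no longer needed would add an unmasked judgement to an observable event. That objection is sound, and the remedy below does not rest on it alone.

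**Conclusion.** The point holds as a fault in a stated definition. As worded, stopping CPAP counts as OSAS remission whatever the reason, and the link to the general definition is not given. Patients who give up CPAP with persisting symptoms can be scored as in remission, and remission is unclear for OSAS patients without CPAP at baseline.

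The likely consequence is overstated OSAS remission in both arms. If stopping is unrelated to arm, a true difference shrinks by the factor (1 − q); if it depends on arm, the bias can go either way. The size cannot be fixed, because the article gives no OSAS prevalence, CPAP use, remission rate or CPAP-stopping rate. The illustrations show only the form of the effect.

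The reach is limited to one of six complications within one secondary outcome. The primary outcome and sample size are unaffected. The correction is worth making because it is cheap and the rule is already in print.

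**What to change.** Reconcile the two definitions in Secondary Outcomes:

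- For patients using CPAP at baseline, score OSAS remission only when CPAP has been discontinued and no OSAS symptoms are reported at that visit.
- Record the reason for stopping at the existing visits (4 months and annually), and do not score stopping for intolerance or non-adherence as remission.
- Classify OSAS patients without CPAP at baseline by the symptom criterion of the general definition.

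This changes how an outcome is scored, not how any patient is treated, and needs no sleep study. The cost is one clause in the definition, one extra data field and somewhat lower reported remission rates. Two limits remain: persisting apnoea without symptoms would still be scored as remission, and symptoms and reasons for stopping are reported by patients who know their allocation.
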